### Analysis

Groups B and C will be combined for comparison with group A for testing of Hypothesis 1. Groups B and C will be compared to test Hypothesis 2. Alcohol consumption will be analysed using negative binomial regression, with baseline AUDIT-C score as a covariate to account for regression to the mean. Hangover incidence and other dichotomous variables will be analysed with logistic regression. Results will be presented as risk ratios and odds ratios. Participants will be analysed in the group to which they were randomised (intention to treat). Analyses will be stratified by centre to account for the multicentre nature of the trial.

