### Screening

The baseline survey will be comprised of questions about alcohol intake and other behaviour (available at http://behaviourscience.net/). Any participant whose answers indicate a moderate to high level of alcohol intake (indicated by a score of 4 or more on the AUDIT-C [15]) will be randomised to one of three conditions. Those who score less than 4 on the AUDIT-C will be thanked for participating and provided with a link to *Alcohol: The Basics*, a page containing information about effects of alcohol, safe drinking levels and problems associated with drinking, such as drink-driving (Figure 2).

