### Outcome measurement

At baseline each participant will be advised they will be sent another survey by email in a month's time. The second survey (which can be viewed at http://behaviourscience.net/) contains eight questions about drinking patterns over the past month and participants' impressions of the study. The primary outcome measures will be the frequency, quantity of alcohol consumption per typical drinking occasion (in standard drinks; 10 g ethanol), volume of alcohol consumed in the preceding four weeks and the incidence of hangover in the same period.

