### Baseline

Most (14/21) of the pilot participants viewed the baseline survey wholly positively. They said they felt comfortable answering the questions and that the survey was well laid out, straightforward, non-invasive, non-ambiguous and well-designed. Negative comments (4/21) included that it was extremely brief and one participant wondered if we should be asking more questions in order to "get a better understanding" of student drinking. Similarly, another participant did not understand what use the survey would be and suggested we include questions about drinking motives and offences relating to alcohol.

In regard to *Alcohol the Basics*, most participants either did not read or skim read the information. Only four made comments about it: one found it 'especially helpful' in regard to limits; two said there was a 'good level of detail' but one of these suggested adding more information. One participant commented they had 'heard it all before'. There were various comments regarding question 4 ("How often do you have a drink containing alcohol?") being unclear and too general.

There were 10 comments specific to randomisation. Six people found the concept of randomisation 'weird', 'confusing' or 'unusual', however, this was not always negative as one said it was 'unusual but OK'. Two of these comments were in regard to being randomised to the control group but receiving information anyway. The other four were positive about the randomisation process saying they 'felt fine' or 'didn't mind' being randomised.

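### Adjusting frequency and typical-occasion quantity only for the AUDIT-C total gives up some precision that a matching baseline answer would recover

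*Protocol article*

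**What the plan says.** The Outcome measurement section names four primary outcomes. The first two are given as "The primary outcome measures will be the frequency, quantity of alcohol consumption per typical drinking occasion"; the other two are "volume of alcohol consumed in the preceding four weeks and the incidence of hangover in the same period".

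The Analysis section gives one rule for the consumption outcomes, a negative binomial model "with baseline AUDIT-C score as a covariate to account for regression to the mean". Hangover falls under a separate sentence that states no covariate: "Hangover incidence and other dichotomous variables will be analysed with logistic regression".

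According to the Screening section, "The baseline survey will be comprised of questions about alcohol intake and other behaviour", and the AUDIT-C also decides entry, since eligibility is "indicated by a score of 4 or more on the AUDIT-C". The article does not list the AUDIT-C items. The Baseline subsection of the pilot work does print one baseline question, number 4: "How often do you have a drink containing alcohol".

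**The concern.** In a randomised comparison, a baseline covariate chiefly buys precision, and it buys most when it measures the same thing as the outcome. Here three different consumption outcomes share one covariate, a composite score. If the composite combines how often and how much a student drinks, a frequent light drinker and an infrequent heavy drinker can share a score. The composite is then a weaker baseline for frequency, or for quantity, than the student's own answer on that dimension.

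The entry rule can sharpen this. Selecting students on a minimum composite score pushes its components towards negative correlation among those randomised, which weakens the link between the score and any one component.

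What is at stake is interval width. The Sample size estimation section aims at differences of 5.5% to 7%, and the number of further students to invite is to be settled after preliminary analyses at the first university. Precision therefore bears on recruitment as well as on the final estimates.

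**Working it through.** **Inputs from the protocol article.** Sample size estimation: power 0.80, two-sided alpha 0.05, dispersion k = 0.2 (alternative 0.4), 1,946 analysed per group (5,838 in total), detectable difference 5.5% (7% at k = 0.4). Screening: entry at AUDIT-C 4 or more. Analysis: AUDIT-C score as the only named baseline drinking covariate.

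**Not in the article, so assumed.** The mean count; the content and scoring of the AUDIT-C items (taken as ordinal answers on frequency, quantity and heavy occasions, then summed); every correlation between baseline and follow-up drinking.

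**Step 1: the plan's own figure.** For a negative binomial rate ratio,

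n per group = (z0.975 + z0.80)² × (1/μ1 + 1/μ2 + 2k) / (ln RR)², with (1.960 + 0.842)² ≈ 7.849.

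- k = 0.2, RR = 1.055, assumed μ1 = 6.2: 7.849 × (0.1613 + 0.1529 + 0.4) / 0.002867 ≈ 1,956, against 1,946 stated.
- k = 0.4, RR = 1.07, assumed μ1 = 6: 7.849 × (0.1667 + 0.1558 + 0.8) / 0.004578 ≈ 1,925.

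Both scenarios fit a mean of about 6, which the article does not state. The formula has no covariate term, so the sample size claims no gain from adjustment and is not in dispute.

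**Step 2: total score against the matching item.** One simulation had 60,000 students, entry at a total of 4 or more, correlation between log frequency and log quantity of 0.2 or 0.5, and baseline-to-follow-up stability of 0.6 or 0.8. It used a linear model for the log outcome. The variance ratio is (1 − R² own item) / (1 − R² total).

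| Stability, correlation | Frequency R²: total / own item | Ratio | Quantity R²: total / own item | Ratio |
|---|---|---|---|---|
| 0.6, 0.2 | 0.032 / 0.250 | 0.775 | 0.204 / 0.248 | 0.945 |
| 0.6, 0.5 | 0.088 / 0.224 | 0.851 | 0.216 / 0.220 | 0.995 |
| 0.8, 0.2 | 0.059 / 0.469 | 0.564 | 0.382 / 0.482 | 0.838 |
| 0.8, 0.5 | 0.158 / 0.437 | 0.669 | 0.409 / 0.455 | 0.922 |

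The total does carry information, mainly about quantity. The effect of selection showed in a separate log-linear simulation (second row of the next table): items uncorrelated among all students correlated at −0.20 among eligible students. There the total correlated 0.19 to 0.40 with follow-up frequency, against 0.40 to 0.54 for the frequency item.

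**Step 3: sensitivity to model and assumptions.** Variance with all separate items divided by variance with the total:

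| Simulation | Frequency | Quantity | Volume |
|---|---|---|---|
| Log-linear, 60,000 students, correlation 0 to 0.5, stability 0.6 to 0.75 | 0.71–0.91 | 0.77–0.94 | 0.94–0.98 |
| Log-linear, 120,000 students, similar ranges | 0.72–0.91 | 0.80–0.95 | 0.95–0.99 |
| Negative binomial with robust variances, noise added to the frequency item | 0.69–0.96 | 0.67–0.92 | 0.97–1.00 |
| Linear model for the log outcome (Step 2) | 0.56–0.83 | 0.83–0.97 | 0.79–0.91 |

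The third row is closest to the planned model. The last row is furthest from it, and is the only one with a material gain for volume. A reduction of roughly 5% to 30% summarises frequency and quantity; the outer limits across rows are 4% to 44% and 3% to 33%.

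**Step 4: what 5% to 30% means.** Suppose the stated 5.5% at 80% power applies under the total-score model, which the article does not say. With variance ratio v, interval width scales by √v, the detectable difference is about 5.5% × √v, and power at 5.5% is Φ(2.802/√v − 1.960).

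- v = 0.95: width × 0.975; detectable difference 5.36%; power Φ(0.915) ≈ 82%; same precision from 1,946 × 0.95 ≈ 1,849 per group.
- v = 0.70: width × 0.837; detectable difference 4.60%; power Φ(1.389) ≈ 92%; same precision from 1,946 × 0.70 ≈ 1,362 per group.

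**The case against.** The strongest reply is that nothing here is wrong. A baseline covariate is named in advance, the adjusted comparison is valid under randomisation, and no stated figure relies on a covariate gain. That stands, and it limits the point to efficiency.

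Several narrower objections also have force. The AUDIT-C items are not printed, and the article does not say that question 4 is one of them. Only frequency is shown as a separate baseline question; a baseline quantity answer is inferred from the use of the AUDIT-C and the mention of intake questions. Pilot participants found question 4 vague, which would reduce its value as a covariate. The negative binomial simulation allowed for a noisy frequency item and still gave a gain, though as little as 4% at the low end.

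A reader might infer that baseline information on every primary outcome is being discarded. The article does not support this: it shows no baseline measure of four-week volume or of hangover, hangover is outside the quoted sentence, and the total retains part of the information.

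A reader might also infer that the regression-to-the-mean rationale is a mistake that damages the analysis. Randomised arms regress equally in expectation, so the group contrasts do not need the covariate for that purpose. But AUDIT-C is the entry variable, and adjusting for it deals with chance imbalance that would regress by follow-up. Rewording the reason would change no result.

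**Conclusion.** The point holds as a minor, free efficiency improvement. The Analysis section fixes a composite as the sole baseline adjustment for outcomes that include frequency, while a separate baseline frequency answer is collected. Using that answer would very likely tighten the frequency comparison, and a matching answer would do the same for quantity if one is held. The plausible gain is roughly 5% to 30% of the variance for each, with little or none for volume under the models closest to the planned one. All four simulations agree in direction for frequency and quantity. The size rests entirely on assumed correlations and an assumed item structure, since the article supplies neither. There is no bias or invalid test, and the stated sample size is unaffected.

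**What to change.** In the Analysis section, state that the frequency and typical-occasion quantity models will each include the corresponding baseline answer as a categorical covariate, where it was collected, in place of or in addition to the AUDIT-C total. Adding it is the safer choice for quantity, because in one scenario above swapping the total for the quantity item alone gained almost nothing (ratio 0.995). The total may stay as the covariate for volume. The hangover model is outside this change.

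The cost is one sentence and a few extra model terms with about 5,800 participants. No new data are needed. The choice should be fixed before outcome data are analysed by group, including the preliminary analyses after the first university.

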### Sample size estimation

There is no previous research on which to base an expected effect size for this study. Assuming power of 0.80, alpha 0.05, dispersion of 0.2, and a 2-sided test, we would need to analyse 1,946 cases per group at 1 month (i.e., a total N of 5838) we could detect a group difference of 5.5% for comparisons of B v C (Hypothesis 2). This sample size provides additional power to detect an effect of similar size for A v B and C (Hypothesis 1). If the dispersion is greater than anticipated at 0.4, with 5,838 participants at follow-up we will still be able to detect a 7% difference. Accordingly, we will invite all students at the University of Otago (approximately 20,000 individuals), with the expectation of recruiting approximately a third of the total required, which is feasible considering a recent survey at that university [16]. We will then conduct preliminary analyses to estimate an effect size and determine the number to be invited from a second university, and whether a third university is needed.

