### Follow-up

There was very little feedback regarding the follow-up survey with over half (11/21) providing no comment. One participant said it was 'extremely short but good'; two thought it connected well to the baseline survey and one said it was similar to the baseline survey. One participant felt uncomfortable answering Question 5 ("What would you say was the design of the study?") but did not explain why. Another person questioned the use of the survey as they did not understand what difference could be shown after four weeks.

All comments and feedback were assessed and the survey was adjusted accordingly. Changes included: adding the demographics questions 1-3 from Baseline (gender, age and living arrangements) to the Follow-up survey; making the drop-down menus larger on screen so respondents did not need to scroll down as far; adding the response option 'don't know' to question 6 of the Follow-Up survey; questions 6 and 7 of the Follow-Up survey were changed from "after completing the survey last month..." to "after completing the previous survey..." as some follow-up surveys would fall in the same month, although four weeks after the baseline survey.

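### The hangover model is given no baseline drinking covariate, although the consumption models adjust for AUDIT-C; adding it costs nothing and recovers some precision

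*Protocol article*

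**What the plan says.** All references are to the protocol article.

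- **Outcome measurement** lists four primary outcomes without ranking them: drinking frequency, quantity per typical occasion, four-week volume, and incidence of hangover over the same four weeks.
- **Analysis** assigns negative binomial regression to alcohol consumption, "with baseline AUDIT-C score as a covariate to account for regression to the mean". The next sentence covers hangover: "Hangover incidence and other dichotomous variables will be analysed with logistic regression". It names no covariate.
- **Analysis** also stratifies all analyses by centre and closes the modelling description with "Results will be presented as risk ratios and odds ratios", without saying which measure goes with which outcome.
- **Screening** randomises only those scoring 4 or more on AUDIT-C, so the score exists for every randomised participant.
- **Sample size estimation** is built on a count model: "Assuming power of 0.80, alpha 0.05, dispersion of 0.2, and a 2-sided test", giving "we would need to analyse 1,946 cases per group at 1 month (i.e., a total N of 5838". It contains no calculation for hangover.

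**The concern.** Two adjacent sentences treat primary outcomes of the same trial differently. One model receives a baseline drinking score and the other receives none, with no reason given. All participants were selected on that score, so the reason offered for using it in the consumption models applies equally to hangover. An analyst who follows the text literally would fit hangover on arm and centre alone.

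What is at stake is efficiency. If AUDIT-C predicts hangover, leaving it out lowers the power of a primary comparison for no saving.

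Adding the covariate raises a reporting matter. The odds ratio from a logistic model moves further from 1 when a prognostic covariate enters, and when the event is common it is already further from 1 than the risk ratio. The sentence on effect measures does not say whether hangover will also get a risk ratio, or how one would be obtained from a logistic fit. If the term was meant for the consumption models, it is the wrong name for what they estimate.

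**Working it through.** **1. The plan's own figure.** For a negative binomial comparison of two equal groups, n per group = (z₀.₉₇₅ + z₀.₈₀)² × [(1/μ)(1 + 1/RR) + 2k] / (ln RR)², where k is the dispersion and μ the mean count. The article does not give μ, so 1,946 cannot be reproduced from the stated inputs alone. It is attainable, however. With μ = 6 assumed:

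- k = 0.2, RR = 1.055: 7.849 × (0.3246 + 0.4) / 0.002867, giving 1,985.
- k = 0.4, RR = 1.07: 7.849 × (0.3224 + 0.8) / 0.004578, giving 1,925.

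Both are within 3% of 1,946, so nothing shows the figure to be wrong. It is used below only as the number per group.

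**2. Power gained from the covariate: asymptotic check.** From the document: 1,946 per group, two-sided alpha 0.05, groups B and C compared 1:1. Assumed: control hangover rates of 0.3, 0.5 and 0.7, and a standardised normal covariate with log odds coefficient c = 0.5, 0.8 or 1.2. The effect is set so that the unadjusted Wald test has 80% power; power is then recomputed with the covariate in the model. The equivalent saving in participants is 1 − [(1.96 + 0.842)/(1.96 + z_adj)]², where z_adj is the normal quantile of the adjusted power.

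| Covariate strength | c-statistic | Adjusted power (from 80%) | Equivalent saving in participants |
|---|---|---|---|
| weak (c = 0.5) | about 0.63 | about 82% | about 5% |
| moderate (c = 0.8) | 0.70 | 84–85% | 11–12% |
| strong (c = 1.2) | 0.77 | 88–89% | 20–22% |

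The result hardly depends on the control rate.

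**3. Power gained: simulation.** Assumed: 1,500 trials per setting, 1,946 per group, AUDIT-C as a rounded normal (mean 7, SD 2.2) clipped to 4–12, hangover about 57%, conditional odds ratio 0.83 for arm.

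| Odds multiplied per AUDIT-C point | Power without AUDIT-C | Power with AUDIT-C | Gain (points) |
|---|---|---|---|
| 1.22 | 81% | 82% | 1 |
| 1.42 | 75% | 79% | 4 |
| 1.65 | 67% | 76% | 9 |

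The two approaches agree on a gain of roughly 1 to 9 points. The top of the range needs a strong predictor. The entry cut-off of 4 narrows the spread of the score, which favours the lower end.

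**4. Effect scale after adjustment.** From the check in step 2 with the moderate covariate:

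| Control rate | Risk ratio | Marginal odds ratio | Conditional (adjusted) odds ratio |
|---|---|---|---|
| 0.3 | 0.866 | 0.818 | 0.799 |
| 0.5 | 0.910 | 0.835 | 0.814 |
| 0.7 | 0.940 | 0.825 | 0.805 |

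At a control rate of 0.5, for example, a 9% lower risk appears as about 19% lower odds in the adjusted model. Both are correct on their own scales, but they are not interchangeable.

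**5. Label.** Negative binomial regression with a log link models the mean of a count. The exponentiated arm coefficient is mean in one group divided by mean in the other. A risk ratio compares probabilities of an event, so the term does not describe that coefficient.

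**The case against.** The strongest reply is that the hangover sentence is silent and does not exclude covariates, and that a condensed article may leave covariate lists to an analysis plan not shown here. This stands in part: the text does not say that the hangover model is unadjusted, and centre is accounted for. But the Analysis section does choose to name a covariate, and does so for one set of primary outcomes only. That asymmetry is in the text.

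It is also true that omitting AUDIT-C does not invalidate a randomised comparison, and that every gain quoted rests on associations the document does not give.

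A reader might go further in four directions that the document does not support:

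- **That hangover is the primary outcome with the least power.** No target effect for hangover is stated, and the answer depends on the scale chosen. At 1,946 per group and control rates of 0.3, 0.5 and 0.7, unadjusted power is 0.20, 0.40 and 0.73 for a 5.5% relative reduction, but 0.97, 0.93 and 0.96 for a 5.5-point reduction. Power for frequency, quantity and volume was not compared.
- **That the odds ratio overstates the effect.** A 5.5% relative reduction from 50%, 60% or 70% does correspond to odds ratios of 0.90, 0.87 and 0.84. This misleads only someone who reads an odds ratio as a risk ratio. No hangover rate is given, and the 5.5% ("we could detect a group difference of 5.5% for comparisons of B v C (Hypothesis 2") belongs to the count calculation.
- **That the odds ratio is the only measure planned for hangover.** The article plans both kinds of ratio and does not assign them to outcomes.
- **That the consumption models should also include gender and a matching baseline drinking item.** Those models already have a baseline drinking covariate, and no gain from adding more has been shown. This would be a preference.

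**Conclusion.** The point holds as a modest one about precision and reporting. As written, the hangover model leaves out a baseline score that the consumption models use and that is available for everyone randomised. The comparison remains valid. The loss is roughly 1 to 9 percentage points of power at 1,946 per group, probably toward the lower end. That range depends on assumed hangover rates and assumed AUDIT-C associations. The difference between adjusted odds ratio and risk ratio matters only if hangover is common, which the document does not establish; it is the reason to pair adjustment with a marginal measure. Calling the negative binomial result a risk ratio is a minor error of labelling.

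**What to change.** In the Analysis section:

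1. State that the logistic model for hangover includes baseline AUDIT-C, together with centre.
2. State that a standardised (marginal) risk ratio or risk difference from that model will be reported beside the odds ratio.
3. Call the negative binomial result a ratio of means (rate ratio), so that each effect measure is tied to its outcome.

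This takes one or two sentences and no new data, and does not change the sample size. It is best settled before the preliminary effect estimates after the first university, which will guide further recruitment.

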### Attrition

Participants who fail to respond to the e-mail invitation to complete the follow-up questionnaire and the reminder two weeks later will be sent an e-mail inviting them to respond to two questions (frequency and typical occasion quantity) within the body of an e-mail message. These responses will be used to determine whether there are differences at baseline between these individuals and those who completed the follow-up by way of investigating attrition bias.

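### Drinking answers e-mailed by follow-up non-responders are assigned to a baseline comparison that they cannot inform, rather than to the follow-up comparison by group that bears on attrition bias

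*Protocol article*

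**What the plan says.** All places are in the Methods of the protocol article.

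- **Attrition.** People who answer neither the follow-up invitation nor the reminder "will be sent an e-mail inviting them to respond to two questions (frequency and typical occasion quantity) within the body of an e-mail message". The use of the replies is then stated: "These responses will be used to determine whether there are differences at baseline between these individuals and those who completed the follow-up". The declared purpose is "by way of investigating attrition bias".
- **Outcome measurement.** Both e-mailed items are primary outcomes: "The primary outcome measures will be the frequency, quantity of alcohol consumption per typical drinking occasion" head the list, followed by four-week volume and hangover.
- **Screening.** "The baseline survey will be comprised of questions about alcohol intake and other behaviour", and only those scoring 4 or more on the AUDIT-C go on to be randomised. Every randomised participant therefore has baseline drinking data.
- **Analysis.** "Alcohol consumption will be analysed using negative binomial regression, with baseline AUDIT-C score as a covariate". Participants are analysed as randomised. The section does not mention the e-mailed answers.

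**The concern.** The stated use does not match the data. Answers gathered after the one-month survey has been missed cannot reveal a difference that existed at baseline. The baseline survey can reveal it, for every non-completer, without any e-mail.

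The mismatch matters because baseline AUDIT-C is already in the regression, so non-response explained by baseline drinking is largely dealt with. What remains is follow-up drinking that differs between non-responders and completers, above all if it differs by group. Baseline characteristics can be balanced while that bias is present. The e-mailed answers are the only information described in the article that bears on it directly, and they are assigned to another question.

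Group-dependent response is plausible here, because the groups differ only in what they are told about the study. In the pilot, six of the ten comments on randomisation found it odd or confusing, and two of these came from being a control yet still receiving information. Group A is told nothing about randomisation.

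**Working it through.** **1. What each comparison can show**

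| Comparison | Data needed | Needs the e-mailed answers? | What it shows |
|---|---|---|---|
| Baseline drinking, all non-completers v completers | Baseline survey | No | Selection on baseline drinking |
| Baseline drinking, e-mail repliers v completers (the stated check) | Baseline survey, plus who replied | Only the fact of a reply | Indirect sign of selective loss |
| Follow-up drinking, e-mail repliers v completers, by group | E-mailed answers and follow-up survey | Yes | Whether outcomes differ by response status and group |

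The content of the answers is needed only in the third row, which the article does not describe.

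**2. The yardstick**

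The Attrition section gives no figure. Sample size estimation gives 1,946 per group (3 × 1,946 = 5,838) to detect 5.5% between B and C, with dispersion k = 0.2, power 0.80 and two-sided alpha 0.05. The mean count μ is not stated, so 1,946 cannot be strictly reproduced. The usual negative binomial formula is

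n = (1.960 + 0.842)² × [1/μ + 1/(μ·RR) + 2k] / (ln RR)².

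With RR = 1.055 it gives 1,984 at an assumed μ of 6 and 1,955 at 6.2. The 5.5% is thus coherent for a mean near 6. It serves below only as a reference size.

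**3. Illustration: unequal non-response**

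All inputs are assumed. There is no true effect and the overall mean is 1 in each group. Non-responders drink f times the responders' mean, and a fraction q does not respond. The completers' mean is then 1/[1 + (f − 1)q], and the proportional bias in the completer ratio is

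1 − [1 + (f − 1)q₁] / [1 + (f − 1)q₂].

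| f | q₁ v q₂ | Ratio | Bias |
|---|---|---|---|
| 1.2 | 20% v 25% | 1.04/1.05 | 0.95% |
| 1.2 | 20% v 30% | 1.04/1.06 | 1.9% |
| 1.5 | 20% v 25% | 1.10/1.125 | 2.2% |
| 1.5 | 20% v 30% | 1.10/1.15 | 4.3% |

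These values take no account of the AUDIT-C adjustment.

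**4. Illustration: what a baseline check would miss**

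Assume 30% non-response in both B and C. Non-responders drink 20% more than responders in C and the same as responders in B, with baseline drinking alike. The completer ratio is 1/(0.7 + 0.3 × 1.2) = 1/1.06 = 0.943, a spurious fall of 5.7%. Neither response counts nor baseline data would show it. Comparing follow-up answers by group could.

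**5. What including the answers could recover**

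Assume 70% response in B and 60% in C, and that a representative 30% of non-responders reply. The completer ratio moves from 0.98 to 0.99 (f = 1.2) and from 0.96 to 0.98 (f = 1.5). The gain is partial.

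**The case against.** A reader might infer several stronger things that the article does not support.

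- **That the answers are left out of the main analysis.** One use is given, but nothing says it is the only one, and the Analysis section does not restrict the data to web completers. A condensed article may leave late replies and missing-data rules to a fuller document.
- **That the check pools the groups.** The section does not say whether the comparison is pooled or by group.
- **That this contradicts intention to treat.** The article uses the term to mean analysis in the assigned group. It does not promise complete outcomes.
- **That attrition bias goes wholly unexamined.** Replying marks a late-responder group whose baseline data can be set against completers'. That is a weak and indirect check, but a real one.

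The magnitude also has limits. Every input is assumed. In step 3, unequal non-response would be visible from simple counts, heavier drinking already present at baseline would show in a baseline comparison, and AUDIT-C adjustment would remove part of the bias. The 4.3% needs both the largest f and the widest gap. Step 4 avoids these points but is equally hypothetical.

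Keeping late answers, given in another mode and with no stated recall period, out of the primary analysis would be defensible. They cover two of the four primary outcomes: hangover is not asked, and volume could only be approximated as frequency times quantity.

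Finally, the reference to baseline may be loose wording for a follow-up comparison. If so, the sentence still needs correcting before outcomes are seen; otherwise the choice of comparison becomes post hoc. None of these points makes the stated use fit the data.

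**Conclusion.** The point holds as a fault in what the Attrition section states. It gives newly collected values of two primary outcomes a task that existing data already perform, and the stated check cannot show whether follow-up drinking differs between non-responders and completers, overall or by group. The article names no other role for these values and does not exclude them.

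The size is unknown, because the documents report no attrition. Under the step 3 assumptions the bias is about 1% to 4% against the 5.5% target, before baseline adjustment. It could reach the target only if non-responders' drinking differs by group, as assumed in step 4.

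**What to change.** Amend the Attrition section to:

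1. Compare baseline data of all non-completers with completers, by randomised group, from data already held.
2. Compare the e-mailed follow-up frequency and quantity with completers' follow-up answers, by randomised group, adjusted for baseline AUDIT-C.
3. Add a sensitivity analysis of frequency and quantity that includes the e-mailed answers in the randomised group, shown beside the web-only result. Use the difference found in item 2 to set a missing-not-at-random sensitivity analysis for those who never reply.

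The cost is revised wording and a little more analysis, with no new data collection. The later timing and different mode of the replies are the reason for using them in a sensitivity analysis. The remedy does not extend to hangover, and it reaches volume only by approximation.
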